**Exclusion Criteria:**

Women over 18 years of age, and unable to give informed consent.

**Enrollment (N=157) and Study Procedures:** Using a simple conjoint experimental task, key preferences will be elicited to address the barriers identified above. Multidimensional scaling and will create a list of closed choice scenarios.

**Sample Size:** Total sample size of 157 young women will be given a short conjoint survey. Sample size considerations will be based on the standard formula for sample size estimation for discrete

choice experiment analysis published by Johnson and Orme. In which, the rule of thumb as proposed by Johnson and Orme (60, 61) suggests that the sample size required for the main effects depends on the number of choice tasks (t), the number of alternatives (a), and the number of analysis cells (c) according to the following equation:  $N > 500c/(t*a)$ , indicating that a minimum sample size of 94 respondents was needed to all two-way interactions. As this rule of thumb is sometimes insufficient, and to allow for sub-group analyses, we will then increase the sample size by 40%, resulting in a targeted sample size of 157 respondents(62).

**Table 1: Examples of Conjoint tasks Post-interviews for Aim 1**

| Characteristics under for conjoint task                                          | Discrete choices                            |
|----------------------------------------------------------------------------------|---------------------------------------------|
| Treatment format                                                                 | Group or individual                         |
| Treatment duration                                                               | 1,2 or 3 hours                              |
| Incentives                                                                       | Food, transport both or care items for baby |
| Treatment setting                                                                | MCH facility, home, community center        |
| Treatment support                                                                | Male partner, mother, aunt or friend        |
| Infant care information                                                          | Yes needed or not needed                    |
| Lifeskills needed (assertiveness skills, simple Maths/accounting/home economics) | Yes needed or not needed                    |
| Delivery of intervention                                                         | MCH nurse, social worker, mental worker     |
| Reading material about depression                                                | Yes or no                                   |
| Links with livelihood support organizations                                      | Yes or no                                   |
| Nutritional training for self and baby                                           | Yes or no                                   |

**Analysis Plan.** Qualitative data (from focus groups and observation) collected under this aim will be transcribed and analyzed using *Atlas.ti*, focusing on barriers/strategies themes related to

- (i) Improving fit of the *mhGAP*-depression intervention model (including IPT-G) for pregnant adolescents; and (ii) enhancing effective integration and implementation of *mhGAP-IG* into MCH settings. Analysis for qualitative data will follow techniques of narrative analysis (63, 64, 65, 66) and a "constant comparison" analytic approach (67, 68) and be carried out by graduate-level students. We will employ content/thematic analysis to assimilate the rich qualitative data. Quantitative data (e.g., knowledge, EBI attitude) will be analyzed using descriptive and multi-level regression analysis. Reliability and validity of the survey measures will be examined, which may be refined and then be used in Aim 3. We will compile a summary of themes/findings and then be presented back to the Advisory Board members for feedback.

**Data Collection and Analysis for the conjoint task:** Brief descriptions of treatment and barrier-stigma-reduction strategies will be read to the participants from a standardized script before the survey is administered. For each pair of scenarios, the participants will be asked to select the one they prefer. Patient characteristics will be examined using standard descriptive statistics.

Multinomial regression will follow binary logit estimates of treatment and barrier-reduction preference parameters through regression analyses. For each regression, the dependent variable will be a binary indicator of treatment acceptance, and independent variables will be the attribute levels and future scenarios. The estimated  $\beta$  coefficients indicate the relative utility of each attribute level, with positive values indicating stronger preference. SAWSOOTH (69) software will be used to analyze the conjoint experiment and SPSS (70) will be used for descriptive statistics and triangulating conjoint findings to different participant attributes. The findings would be integrated in the Aim 2 adaptation process.

To carry out a psychometric evaluation of brief depression, anxiety, suicidality and general functioning tools with general sample of adolescents and pregnant adolescents to develop more sustainable assessments in primary care

We intend to add a short exercise of pilot testing of a set of brief tools that have been recommended for MICS data collection on mental health indicators for adolescents in LMICs. These tools are briefer, simpler and currently being tested with adolescents in Belize and South Africa. These tools cover depression, anxiety, suicidality and functional impairment using Revised Children's Anxiety and Depression Scale (RCADS) (71)

We will test these tools on ages 10-14 and 15-19 years in our study sites. The tools which were listed as part of the intervention have been developed for adults though tested on adolescents.

The overall aim of this exercise is to establish the validity and reliability of measures of adolescent mental health, using multiple qualitative and quantitative approaches, including focus groups, translation/back translation, clinical evaluation, and psychometric analyses.

The specific objectives are

1a) Examine the content validity of tool items within each of the tools for the Kenyan context, using focus group discussions and interviews, and appropriateness of items using cognitive interviewing techniques.

1b) Validate the key measures of mental health for adolescents for a questionnaire module against a gold standard diagnostic interview and classical and modern psychometric analyses.

2: Explore mental illness stigma, help seeking behavior, perspectives on access to social support, mental health care or social services utilization, and knowledge about mental health, using focus groups.

3: Understand younger and older adolescents' conceptions of mental health and wellbeing and how proposed intervention materials can be adapted to best suit Kenyan adolescents, and how materials could be adapted for pregnant and parenting adolescent populations in various LMIC settings.

Table 1b: questionnaire testing phases, steps and relevant activities

| Phase                         | Step | Activity                                                                                                                                                                                                |
|-------------------------------|------|---------------------------------------------------------------------------------------------------------------------------------------------------------------------------------------------------------|
| 1. Adaptation and Pre-testing | 1    | Adaptation of the English-language tools by a local team of 3 with language expertise to ensure appropriateness for the Kenyan context                                                                  |
|                               | 2    | Review by 3 local mental health experts (independently) and discussion as a team                                                                                                                        |
|                               | 3    | Focus group discussions with 6 target adolescent groups: boys ages 10-14, boys 15-19, girls 10-14, girls 15-19, or 3 younger and 3 older adolescent groups (6 groups of 6-8 adolescents, (n=48)         |
|                               |      | Focus group discussions with parents of 10-19-year-olds (2 groups of 6-8 parents, n=16)                                                                                                                 |
|                               | 4    | Back translation (by individual blind to original version of tool)                                                                                                                                      |
|                               | 5    | Cognitive Interviewing with 2 adolescents in each of the 4 target groups above (n=8) and with parents of children ages 10-19 (n=8) and qualitative analyses of the cognitive interviewing, (total n=16) |
| 2. Administration of the tool | 6    | Administration of the tool among selected sample of adolescents and parents of younger adolescents (n=250 adolescents (125 adolescents per site), n= 100 caregivers (50 parents per site)               |
| 3. Validation                 | 7    | Validation using diagnostic interview by trained mental health worker/ psychosocial counselors in both sites. Eight trained mental health workers will be used (4 per site)                             |
|                               | 8    | Statistical analyses to establish psychometric properties of the measures will follow the same procedure as the tools given in the proposal.                                                            |

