### 3.3 Methodology for Aim1

(Study barriers and strategies to improve mhGAP-IG/IPT-G fit and implementation).

To understand ‘fit’ of the mhGAP/IPT-G and study multi-level barriers/strategies to promote utilization and impacts of IPT-G and mhGAP, we will carry out a mixed methods study, including qualitative and quantitative data collection. Quantitative data collection will focus on D&I readiness contexts and new D&I tools pilot testing, which will be used for Aim 3 evaluation study.

**Data Collection Focus and Procedures:** We will conduct 8 focus groups (n=40) with representative diverse stakeholders (i.e., including 2 groups for pregnant adolescents and new adolescent mothers, 2 groups for adolescent caregivers and partners, 2 groups for MCH staff, 1 group for community advocates and policy leaders, and 1 group for child and adolescent mental health professionals). Each focus group discussion (FGD) will have about 5 participants. Each group will participate in three FGD meetings. One meeting will focus on barriers/strategies related to mhGAP-IG, and the other meeting will focus on barriers/strategies related to IPT-G. The third FGD would be focusing on mental health treatment preferences of pregnant adolescents. Each focus group will last 1½ to 2 hours. Participants will participate in a FGD and complete a survey, and these will be carried out in English or Kiswahili (as English is the official language in Kenya). Focus group guides/questions and quantitative survey will be adapted from existing D&I studies (57), or existing D&I measures (see measures under Aim 1). Stakeholders’ views on barriers and strategies in 5 CFIR domains (see Figure 2 second left box) will be discussed separately for mhGAP and IPT-G. Informed by our previous need assessment work, strategies related to livelihood problem, partner/family engagement, knowledge gap, and stigma reduction will also be explored.

- For focus group with *adolescents and families/partners* (n=20, recruited through 2 MCH clinics that we have partnership with from previous MCH epidemiological studies), discussion will focus on CFIR individual, intervention, and inner setting domains, and examine their knowledge related to perinatal depression, and views (including barriers and potent

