ial strategies) related to adolescent pregnancy, mhGAP/IPT-G (fit, usefulness, perceived feasibility and effectiveness of IPT-full and mini versions), family member/partner engagement, support, and empowerment strategies, and preference for integrated mental health-MCH services. See appendix.

- *For the MCH providers/staff and mental health professionals (n=15, recruited through 2 MCH clinics [same as the sites for family recruitment] and mental health professional networks)*, discussion will focus on the CFIR inner setting, individual/staff, intervention, and process domains. We will examine fit, barriers, and implementation strategies for mhGAP and IPT-G implementation in MCH settings (e.g., collaborators' roles, task-shifting/sharing strategies, workflow logistic/coordination strategies), staff attitude/belief toward EBI practices, perceive effectiveness, and MCH implementation climate. See appendix.
- *For the community advocates and policy stakeholders (n=5, recruited through Ministry of Health and NGO networks)*, discussion will focus on the CFIR intervention, process and outer setting domains, and examine barriers and strategies related to mhGAP and IPT-G. In addition, community awareness/public educational and stigma reduction strategies (outer setting strategies) will be explored to facilitate community support to address adolescent pregnancy and maternal mental health needs, which also has implications for public health impact promotion (58, 59). See appendix.

**To better identify mhGAP/IPT-G workflow barriers and strategies in MCH contexts**, MCH site visits and workflow observation will be arranged for the Community and Technical Advisory Board members (n=18, including researcher). The observation will focus on MCH structure and perinatal service workflow. This will allow the Board and research members to gain better understanding about the clinical setup, implementation barriers and strategies, which will facilitate better and more sustainable workflow plan/strategy development to support mhGAP/IPT-G implementation. To ensure confidentiality, informed consent for all participants will be obtained prior to the data collection. Participating provider personnel and family members will be compensated for their time. Participating mental health professionals and officers of NGO/ Ministry of Education/ Ministry of Health will also be compensated.

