### 3.7 Study Participants

A total of 1234 subjects will participate in this study (across 3 study aims).

**Aim 1: Participants for studying “fit” of the mhGAP/IPT-G and understanding multi-level barriers/strategies (Aim 1; n= 80 diverse stakeholders).** To study potential barriers and strategies for promote utilization and impacts of IPT-G and mhGAP, we will conduct 8 focus groups with representative diverse stakeholders (i.e., including two groups for pregnant adolescents and new adolescent mothers, two groups for adolescent caregivers and partners, two groups for MCH staff, one group for community advocates and policy leaders, and one group for child and adolescent mental health professionals).

**Aim 2: Implementers for mhGAP/IPT-G intervention (Aim 2; n=36 provider subjects).** To build research capacity, we will provide a short/intensive course on child mental health implementation methodology for research team members, relevant stakeholders, and graduate level students (n=20 in year 2). To build service capacity for adolescent perinatal depression, we will train MCH implementation team (n=16 from 2 MCH clinics) for task-shifting/sharing collaborative approach of mhGAP-IG and IPT/G implementation. Quality and impacts of training will be assessed through attendance tracking, after training satisfaction evaluation, pre- to post-training knowledge/competence assessment with trainees.

**Aim 3: Participants for mhGAP/IPT-G intervention Evaluation Study (Aim 3; n= 90 pregnant adolescent subjects).** To estimate impacts of the intervention, 90 adolescents and their caregivers from 2 MCHs will be recruited for the intervention evaluation study.

Inclusion criteria. (For the feasibility study)

- Pregnant adolescents (ages 13-18)
- Screened with moderate to severe depression during the 1st to 2nd trimester (defined as Edinburgh Postnatal Depression Screen (EPDS) score  $\geq 13$  or meet the APA's Diagnostic and Statistical Manual for Mental Disorders IV-TR version (DSM-IV-TR) criteria for major depression disorder and perinatal depression).
- Who agree to give informed consent (by adolescents and their adult caregivers)
- Are willing to come for group sessions at MCH clinic, and
- Can participate in evaluation assessment will be eligible.

Exclusion criteria

Participants will be excluded from the study if they:

- Suffered from or showed evidence of severe personality disorder, acute psychosis, suicidality, or

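### Aim 1 plans multi-level regression and psychometric refinement of survey measures on 8 small focus groups whose total is given as both 40 and 80; staff-only scales would have about 15 respondents

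*Protocol*

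**What the plan says.** Protocol section 3.3, under data collection, sets the Aim 1 sample: "We will conduct 8 focus groups (n=40) with representative diverse stakeholders". It adds: "Each focus group discussion (FGD) will have about 5 participants". The same people supply the quantitative data: "Participants will participate in a FGD and complete a survey".

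The groups are two of pregnant adolescents and new adolescent mothers, two of caregivers and partners, two of maternal and child health (MCH) clinic staff, one of community advocates and policy leaders, and one of child and adolescent mental health professionals. By recruitment stream, adolescents and families number 20 ("n=20, recruited through 2 MCH clinics that we have partnership with from previous MCH epidemiological studies"), staff and professionals 15 ("MCH providers/staff and mental health professionals (n=15"), and advocates and policy stakeholders 5.

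The purpose is stated in the same section: "Quantitative data collection will focus on D&I readiness contexts and new D&I tools pilot testing, which will be used for Aim 3 evaluation study". Its Analysis Plan says that data such as knowledge and attitude to evidence-based interventions (EBI) will receive descriptive and multi-level regression analysis, and continues: "Reliability and validity of the survey measures will be examined, which may be refined and then be used in Aim 3".

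Section 3.7 describes the same 8 focus groups with a different total: "Aim 1; n= 80 diverse stakeholders".

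**The concern.** The protocol fixes both the analysis and the sample, and they do not fit. Multi-level regression needs enough groups to estimate variation between groups. Reliability and validity estimates that feed into scale revision need enough respondents for the item statistics to reflect the items and not the particular people sampled. Section 3.3 gives no sample rationale for this survey. The separate validation exercise for adolescent mental health tools in the same section does discuss its sample size, plans 250 adolescents, and names a reliability benchmark of 0.80. It concerns other instruments and adds no respondents to the staff scales.

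At stake are the staff measures carried into Aim 3. If items of an existing scale were dropped or rescored on unstable statistics, comparability with that scale would be lost without evidence of improvement. The conflicting totals also leave the precision of every Aim 1 survey estimate undetermined.

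**Working it through.** **1. Head count.** 8 groups × 5 = 40, and by stream 20 + 15 + 5 = 40. Section 3.3 is therefore internally consistent. The 80 in section 3.7 does not follow from these inputs; it would need groups of 80 / 8 = 10.

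**2. Respondents for staff-only measures.** Two MCH staff groups and one professional group: 3 × 5 = 15, of whom 2 × 5 = 10 are MCH staff. If 80 were right, the pro rata figure is 80 × 15/40 = 30.

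**3. Precision of alpha.** The protocol gives neither item counts nor expected reliability. Assume k = 10 items and observed alpha 0.80. Feldt's 95% interval is 1 − (1 − alpha) × F, with F the 97.5% point (lower limit) and the 2.5% point (upper limit) on n − 1 and (n − 1)(k − 1) degrees of freedom.

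| n | df | F 97.5% | F 2.5% | 95% CI |
|---|---|---|---|---|
| 15 | 14, 126 | 1.972 | 0.392 | 0.61 to 0.92 |
| 30 | 29, 261 | 1.633 | 0.542 | 0.67 to 0.89 |
| 40 | 39, 351 | 1.535 | 0.595 | 0.69 to 0.88 |

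Example at n=15: 1 − 0.20 × 1.972 = 0.61. For items that only the 10 MCH staff can answer, the interval is 0.54 to 0.94. With 5 items instead of 10, the n=15 interval is 0.58 to 0.92, so item count changes little here.

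**4. Precision of a validity correlation.** Assume r = 0.50. Fisher's interval is tanh(0.549 ± 1.96/√(n − 3)). At n=15 the half-width is 0.566, giving −0.02 to 0.81. At n=30 it is 0.17 to 0.73, and at n=40 0.22 to 0.70.

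**5. Item-deletion statistics when no item is bad.** Simulate k equally good items with a common inter-item correlation of alpha/(k − alpha(k − 1)); for alpha 0.80 and k = 10 this is 0.80/2.8 = 0.286. Count the samples in which deleting at least one item raises the sample alpha.

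| Scale | n=15 | n=30 | n=40 |
|---|---|---|---|
| 10 items, alpha 0.80: any rise | about 94% | about 75% | about 61% |
| 10 items, alpha 0.80: rise above 0.01 | about 66% | about 30% | about 18% |
| 10 items, alpha 0.90: any rise | about 78% | about 41% | about 25% |
| 5 items, alpha 0.80: any rise | about 70% | about 40% | about 27% |

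Repeat runs differ by a point or two. At n=15 a false flag is the usual result in every scenario. At n=40 it is frequent in the base case and occurs in about a quarter of samples in the others.

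**6. Group structure.** By type the groups number 2 + 2 + 2 + 1 + 1 = 8. If focus group is the cluster and type the predictor, 8 − 5 = 3 degrees of freedom remain between groups. Two types, community and policy stakeholders and mental health professionals, have one group each, so for them a type difference and a group difference are the same quantity. For staff-only scales there are 3 groups. A total of 80 in the same 8 groups would change none of this.

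**The case against.** The strongest reply is that the text commits to little. Refinement is optional, the work is called pilot testing, and no alpha threshold or item-deletion rule is set. Themes go to the Advisory Board for feedback, so any refinement could rest on comprehension and content. This stands. A reader might infer that scales will be changed on noise; the protocol supports only that they could be, because refinement directly follows the reliability and validity step and nothing prevents it.

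A reader might also infer that no more than 15 people can answer the staff scales. The documents do not settle that. Section 3.7 gives 80, and the contents list a separate consent for a health-worker baseline survey (Appendix 5) whose respondents might contribute. Nor is knowledge clearly a staff scale: section 3.3 also examines knowledge of perinatal depression in adolescents and families. For scales that all members answer, n=40 applies and the noise is milder.

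The levels and predictors of the regression are unspecified and may properly be left to an analysis plan, so the 3 degrees of freedom rest on an assumed model. The narrower point remains: with 8 groups, two of them the only one of their type, no choice of model separates type from group for those two.

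Finally, the survey is to be adapted from existing measures and includes new tools, so original scoring cannot be required throughout. That limits the remedy to items of existing scales.

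**Conclusion.** The point holds in limited form. Section 3.3 names a regression that 8 groups cannot support for comparing stakeholder types, and it leaves open a statistical route to changing measures on too few respondents. Sections 3.3 and 3.7 contradict each other on the total, 40 against 80.

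The imprecision is severe for staff-only measures at about 15 respondents, substantial at about 30, and moderate for scales answered by all 40. These sizes rest on assumed values: alpha 0.80 (0.90 also tried), 10 items (5 also tried) and a validity correlation of 0.50.

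It would be wrong to conclude that the trial's depression result is threatened. In Table 3 the attitude scale and readiness questionnaire are Time 1 context measures, and organisational climate is a service outcome at Times 1 and 2. The listed implementation outcomes are fidelity, engagement and satisfaction; the depression scales are separate. The consequence is confined to staff context and service-climate measures.

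**What to change.** - Reconcile the Aim 1 totals in sections 3.3 and 3.7. Eight groups of about 5 give 40; if 80 is intended, restate the group size and the recruitment numbers to match. If the health-worker baseline survey contributes respondents, say so and give its number.
- In the section 3.3 Analysis Plan, replace the multi-level regression with descriptive summaries by stakeholder type.
- Report reliability and validity estimates with confidence intervals and the number of respondents for each scale.
- State that no item of an existing scale will be dropped or rescored on Aim 1 statistics alone, and that refinement will be limited to comprehension and content feedback from the focus groups and the Advisory Board.

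The cost is protocol wording and the loss of an exploratory regression that could not have been interpreted. No additional recruitment is needed.
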